### Statistical analysis

The primary efficacy analysis will be conducted on an intention-to-treat basis. An as-treated analysis will also be implemented for secondary analyses if a large number of infants do not end up getting the treatment to which they were assigned. Clinical characteristics of infants in the “IN-REC-SUR-E” and “IN-SUR-E” groups will be described using mean values and standard deviation, median value and range, or rate and percentage. Univariate statistical analysis will be performed using the Student’s *t* test for parametric continuous variables, the Wilcoxon rank-sum test for non-parametric continuous variables, and Fisher’s exact test for categorical variables. A *p* value <0.05 will be considered statistically significant. Then, treatment arm and clinical characteristics which are most likely associated with the need for mechanical ventilation (gestational age, birth weight, antenatal steroids, CRIB score) will be included in a multiple logistic regression analysis to assess their independent role in predicting the clinical outcome. Effect estimates will be expressed as odds ratios (ORs) with maximum likelihood-based 95 % confidence limits. An interim analysis will be planned when 50 infants will be enrolled in each arm. The analysis will intend to compare treatment arms with respect to efficacy, safety, futility, assessment of difficulties with patient enrollment, and, if necessary, a sample size adjustment. In the interim analysis for safety the pre-specified stopping rules are: a mortality rate more than 40 %, a rate of severe IVH more than 30 % and a pneumothorax rate of more than 10 %. The interim-analysis will be performed by an independent statistician, blinded for the treatment allocation. The statistician will report to the independent Data and Safety Monitoring Board (DSMB). The DSMB will have unblinded access to all data and will discuss the results of the interim-analysis with the Steering Committee in a joint meeting. The Steering Committee will decide on the continuation of the trial and will report to the central Ethics Committee.

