### Sample size

We hypothesized that a recruitment maneuver (in HFOV modality) before surfactant administration might decrease of the need of subsequent mechanical ventilation during the first 72 h of life from 50 % [2, 5, 7] to 30 %. We calculated that 103 newborns must be enrolled in each group to detect this difference as statistically significant with 80 % power at the 0.05 alpha level using the two-sided Pearson’s chi-square test.

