### Secondary outcome measures

 Duration (days) of nCPAP, need and duration of bi-level NCPAP (BiPAP) and nasal intermittent MV (N-IMV) Need and duration (days) of conventional mechanical ventilation (synchronized intermittent mandatory ventilation (SIMV), synchronized intermittent positive pressure ventilation (SIPPV), pressure support ventilation (PSV) with or without volume guarantee (VG)) or high-frequency oscillatory ventilation (HFOV) with or without VG Duration (days) of oxygen therapy and highest FiO_2_ level of oxygen concentration Duration of hospitalization Number of doses of surfactant during hospitalization Occurrence of mild, moderate, and severe bronchopulmonary dysplasia (BPD) during hospitalization. The severity of BPD is categorized according to the consensus definition [21]: treatment with oxygen >21 % for at least 28 days, plus: mild BPD: breathing room air at 36 weeks post menstrual age (PMA) or discharge, whichever comes first; moderate BPD: need for more than 30 % oxygen at 36 weeks PMA or discharge, whichever comes first; severe BPD: need for at least 30 % oxygen and/or positive pressure (PPV or nCPAP) at 36 weeks PMA or discharge, whichever comes first Time of being without any respiratory support

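### The general rule sends graded BPD severity to Fisher's exact test, which ignores the order of the grades if BPD is analysed as one four-level variable; naming an ordered analysis is a minor improvement to a secondary outcome

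*Protocol article*

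**What the plan says.** Under Secondary outcome measures, the protocol article lists "Occurrence of mild, moderate, and severe bronchopulmonary dysplasia (BPD) during hospitalization" and adds that severity is graded by a cited consensus definition. The grades depend on respiratory support at 36 weeks' postmenstrual age or discharge. No BPD is not named as a level, but it is the implied lowest one.

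Under Statistical analysis, tests are chosen by type of variable: the t test for parametric continuous variables, then "the Wilcoxon rank-sum test for non-parametric continuous variables, and Fisher’s exact test for categorical variables". The significance threshold follows: "value <0.05 will be considered statistically significant". No trend, rank or proportional-odds method is named for ordered categories. The only model described is a logistic regression for the need for mechanical ventilation.

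The section does not mention BPD. It does not say whether BPD is to be tested as one graded variable or as separate yes/no outcomes. The article gives no BPD rate, target effect or power. The Sample size section concerns mechanical ventilation only.

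**The concern.** A graded severity scale carries information in its order. Fisher's exact test on a table of two arms by four grades gives the same p value however the grades are relabelled. A consistent move towards milder disease therefore counts no more than any other rearrangement of the same size, and the power is spread over three degrees of freedom. A significant result also does not itself say in which direction severity moved.

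The Background presents less ventilator-induced injury as a route to less BPD, so a shift in severity is a result that readers will look for. The trial was sized for a different endpoint. Any information on BPD is therefore limited, and it is worth using a test that can draw on the grading.

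**Working it through.** **1. The plan's own figure.** The Sample size section sets 50% against 30%, with "80 % power at the 0.05 alpha level using the two-sided Pearson’s chi-square test", and gives 103 per group. The usual two-proportion formula is n = [1.96·√(2·0.4·0.6) + 0.842·√(0.5·0.5 + 0.3·0.7)]² / 0.2² = (1.358 + 0.571)² / 0.04 ≈ 93. The continuity correction is (n/4)·[1 + √(1 + 4/(n·0.2))]² = 23.25·(1 + √1.215)² ≈ 102.8, so 103. The stated figure reproduces. Exact power at 103 per arm is 84.7% for Pearson's chi-square and 81.1% for Fisher's test. The primary outcome is not in question here.

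**2. Inputs for BPD.** From the article: 103 per arm, 1:1 allocation, two-sided 0.05. Assumed, because the article does not give them: the control-arm distribution over none/mild/moderate/severe, the effect, and a grade for every infant.

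**3. Model of the effect.** Under a proportional shift, each cumulative odds is multiplied by one common odds ratio (OR). Example with control 40/30/15/15% and OR 2.0:
- Cumulative control: 0.40, 0.70, 0.85, so odds 0.667, 2.333, 5.667.
- Doubled: 1.333, 4.667, 11.333, so cumulative 0.571, 0.824, 0.919.
- Treated arm: 57.1/25.2/9.5/8.1%.

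**4. Power for that control distribution.** These come from 40,000 simulated trials per row. The unordered test is the 3-df chi-square, whose power was within 0.5 points of the exact Fisher test in a separate set of 1,200 trials per scenario.

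| Common OR | Unordered | Rank-sum, tie-corrected | Difference (points) |
|---|---|---|---|
| 1.3 | 11.5% | 17.5% | 6.0 |
| 1.5 | 22.8% | 34.8% | 12.0 |
| 1.75 | 40.6% | 57.0% | 16.4 |
| 2.0 | 58.4% | 74.8% | 16.3 |
| 2.33 | 77.2% | 89.2% | 12.0 |
| 3.0 | 94.4% | 98.4% | 4.0 |

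**5. Range over assumptions.** Six control distributions were tried: 50/20/15/15, 40/30/15/15, 60/20/10/10, 25/25/25/25, 30/35/20/15 and 70/15/10/5%.
- OR 1.5 to 2.33: loss of 9 to 18 points.
- OR 1.3: 4 to 6 points.
- OR 3: 3 to 14 points.

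**6. Analytic check.** Give a 1-df test and a 3-df test the same non-centrality. At 6.17, the 1-df test has 70% power and the 3-df test 53.1%, a gap of 16.9 points. When the 1-df test has 30 to 90% power, the gap is 10 to 17 points.

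**7. Where the sign changes.** Take control 40/30/15/15% against treated 45/35/15/5%. The cumulative proportions go from 40 to 45, 70 to 80 and 85 to 95%, so treatment is better at every cut. The odds ratios at the three cuts are (45/55)/(40/60) = 1.23, (80/20)/(70/30) = 1.71 and (95/5)/(85/15) = 3.35, so the benefit is concentrated on severe BPD. Power is 51% for the unordered test and 31% for rank-sum. In the extreme case where infants move only from severe to moderate (40/30/25/5%), it is 64.5% against 6.8%.

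**The case against.** The strongest reply is that the article does not fix a four-level Fisher test at all. The rule is one generic sentence that does not name BPD, and the list of grades could equally mean separate yes/no occurrences, for which Fisher's test is ordinary. The full protocol or an analysis plan may specify more. This stands in part: the four-level test is an inference, and the power figures apply only to it. It does not remove the point, because the published rule covers the variable and offers nothing for ordered categories. Separate cuts also lose information under a proportional shift. At OR 2.0, over three assumed control distributions, a two-by-two Fisher test has 58 to 64% power for any BPD and 36 to 55% for moderate or severe BPD, against 66 to 77% for rank-sum.

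A second reply is that neither test is better for every effect. That stands, as step 7 shows.

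A third is that absolute powers are overstated, because infants who die before grading have no grade. That also stands.

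A reader might infer more than the documents support:
- That the plan loses a fixed amount of power. It does not, since no BPD rate or effect is given.
- That BPD severity is the trial's main longer-term outcome. The article lists it among several unranked secondary outcomes.
- That Fisher's test is invalid here. It controls the type I error.
- That the direction of effect would be hidden. The article provides for rates and percentages as description, so the direction would be visible.

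**Conclusion.** The point holds as a minor improvement. The grades are ordered, the only applicable rule is a test that disregards order, and a better-suited test is already named in the same sentence for continuous variables. If BPD is one four-level variable and the effect is a proportional shift of moderate size (common OR about 1.5 to 2.3), the unordered test gives up about 9 to 18 points of power with 103 graded infants per arm. For smaller or larger effects the loss is often only a few points. If the benefit is concentrated on severe BPD, the unordered test can be the more powerful one. The case for the change therefore rests on expecting a shift along the whole scale.

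The order itself is not yet well defined. The article has "moderate BPD: need for more than 30 % oxygen at 36 weeks PMA or discharge, whichever comes first" and "severe BPD: need for at least 30 % oxygen and/or positive pressure (PPV or nCPAP) at 36 weeks PMA or discharge, whichever comes first". An infant needing more than 30% oxygen meets both definitions. An infant on supplemental oxygen below 30% without positive pressure meets neither, and does not meet the mild definition, which requires room air.

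The primary analysis and the sample size of 206 are not affected.

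**What to change.** First, reconcile the moderate and severe cut-offs under Secondary outcome measures so that every infant falls in exactly one grade, and state how infants who die before grading enter the comparison.

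Then add to Statistical analysis: BPD severity (none, mild, moderate, severe) is compared between arms with the tie-corrected Wilcoxon rank-sum test, and the effect is reported as a common odds ratio with 95% CI from a proportional-odds logistic model. Keep Fisher's exact test for binary and unordered variables. Show the number and percentage in each grade by arm, so that readers can judge whether the proportional-odds summary is reasonable.

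The cost is a sentence or two on the analysis plus the two clarifications, with no extra infants, visits or data. The downside is a loss of power, possibly larger than the gain, if the effect is confined to one grade, and reliance on proportional odds for the summary estimate.

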### Inclusion criteria

Infants satisfying the following inclusion criteria will be eligible to participate: In-born at 24^+0^–27^+6^ spontaneously breathing at birth but requiring respiratory support (CPAP or O_2_) at 5 min of life Parental consent has been obtained Failing nCPAP during the first 24 h of life

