### Exclusion criteria

 Severe birth asphyxia or a 5-min Apgar score <3 Endotracheal intubation in the delivery room for resuscitation or insufficient respiratory drive according to AAP guidelines [16]. Prolonged premature rupture of membranes (PROM) for more than 3 weeks Presence of major congenital malformations Hydrops fetalis Inherited disorders of metabolism

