### Randomisation

Infants will be allocated to one of the two treatment groups in a 1:1 ratio according to the minimization method, using an interactive web-based electronic system. Randomization will be stratified by center and gestational age (24^+0^–25^+6^ weeks or 26^+0^–27^+6^ weeks). A monthly accrual report about the study will be sent to the participating centers.

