
There are some limitations in our study design: (1) surfactant replacement therapy involves instillation of a liquid-surfactant mixture directly into the lung airway tree. Thus, surfactant distribution and efficacy are not only affected by lung recruitment before its administration but also depend on the methodology used for delivery of the drug and on the post-administration ventilatory management (prevention of collapse due to inadequate weaning). In our study, different methods of surfactant delivery will be used between the two groups. In the group of infants submitted to a lung recruitment maneuver, surfactant will be delivered into the airways without disconnection from the high frequency ventilator. The control group will receive surfactant while manually ventilated. On the other hand we cannot recruit and stabilize the lung if we start positive pressure ventilation in the IN-REC-SUR-E group, just to recruit at the time of administration of surfactant and delivery of positive pressure ventilation before/after its use. Recruitment is a conceptual design usually applied from start to finish. The fact that during IN-SUR-E we conventionally ventilate the baby and during HFOV we do not is inherent to the design of the study. If we would ‘bag’ the baby, recruitment will be lost and we will lose the contrast between the groups (administer surfactant in recruited or non-recruited lung). It is more an “open lung ventilation” that is tested against conventional positive pressure ventilation. Open lung ventilation includes surfactant administration in a recruited lung and avoiding injury after administration. The difference in ventilation during and after surfactant treatment is part of optimal lung volume strategy. This makes our study more of a “comparative effectiveness research” comparing two distinct approaches that consist of several components, rather than a simple randomized controlled trial (RCT) comparing surfactant with and without a recruitment maneuver; (2) failure of CPAP therapy is multifactorial. Local experience with this therapy in the smallest patients and type of CPAP applied seems to play an important role in outcomes. Based on the results of a recent survey on the neonatal respiratory support strategies in the Italian NICUs [33], nCPAP is the most commonly used non-invasive mode of respiratory support, both in the acute and post-extubation phases of RDS. The most commonly used devices in delivering non-invasive respiratory support are the Infant Flow® System (56 %), mechanical ventilators (33 %), and bubble CPAP (16 %). All the 37 NICUs involved in the present study have considerable experience with non-invasive respiratory support. Even though there could be potentially different outcomes according to the different devices used to deliver non-invasive respiratory support pre and post extubation, this should not affect the differences between the two interventions in our study, because of the randomization; (3) some studies do show a reduction in intubation need when N-IMV is used after extubation. Even though there could be potentially different outcomes according to the different non-invasive respiratory strategies used after extubation, it is conceivable that clinicians will apply a specific non-invasive ventilatory support (CPAP or BiPAP or N-IMV) similarly in both groups. Although there might be differences between centers, it will be similar within centers and because we randomize on center, this will not affect the differences between the two groups.

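### Siblings can be enrolled and tend to be split between arms, but the stated tests treat all infants as independent; for the treatment comparison the error is small and conservative

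*Protocol article*

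**What the plan says.** - **Eligibility (Inclusion and Exclusion criteria).** The unit is the infant: "Infants satisfying the following inclusion criteria will be eligible to participate". Infants must be "In-born at 24^+0^–27^+6^ spontaneously breathing at birth". The exclusions cover asphyxia or a low Apgar score, delivery-room intubation, long membrane rupture, malformations, hydrops and metabolic disorders. Multiple birth is not among them, and there is no limit of one infant per mother.
- **Allocation (Randomisation).** "Infants will be allocated to one of the two treatment groups in a 1:1 ratio according to the minimization method". The factors are given as "Randomization will be stratified by center and gestational age", the latter in two bands.
- **Analysis (Statistical analysis).** Univariate comparisons use Student's t test, "the Wilcoxon rank-sum test for non-parametric continuous variables, and Fisher’s exact test for categorical variables". A multiple logistic regression on treatment arm, gestational age, birth weight, antenatal steroids and CRIB score follows, with maximum-likelihood 95% limits for the odds ratios. No pairing, family cluster or random effect is named.
- **Data (Other collected data; Data collection).** The listed items include neither plurality nor a link to the mother, and infants are identified by a trial number alone.

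**The concern.** Siblings share a mother, a gestation, usually the antenatal steroid exposure, and a unit, so their outcomes are likely to be positively correlated. Siblings from one delivery also share both minimization factors. Once the first is allocated, the imbalance in that center and gestational-age band favors the opposite arm for the second.

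A pair split between arms acts like a small matched comparison: what the siblings have in common cancels in the treatment difference. Tests for independent infants give no credit for this, so they report a standard error that is too large. At stake is the accuracy of the p-values and confidence limits for the primary outcome, and of the reported role of the family-level predictors in the regression. The estimate of treatment effect itself is not put in doubt.

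**Working it through.** **1. The plan's own figure.** Inputs from Sample size: need for ventilation "from 50 % [2, 5, 7] to 30" %, 80% power, two-sided 0.05.

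n = [1.96·√(2·0.4·0.6) + 0.842·√(0.25 + 0.21)]² / 0.2² = 93 per arm. With the continuity correction, (93/4)·[1 + √(1 + 4/(93·0.2))]² = 102.8, so 103. The stated 103 per arm is reproduced. Both formulas assume independent infants.

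**2. Variance with sibling pairs.** Let n be infants per arm, f the share of infants in enrolled pairs (so f·n pairs), ρ the within-pair correlation and q the share of pairs split. With a common outcome variance σ², each split pair adds −2ρσ²/n² to the variance of the difference and each same-arm pair adds +2ρσ²/n². Hence

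variance = (2σ²/n)·[1 + f·ρ·(1 − 2q)].

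The bracket is the true variance divided by the independence variance.

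**3. How many pairs are split.** Minimization was simulated with 206 infants, two gestational-age bands and the 37 centers given in the Discussion ("All the 37 NICUs involved in the present study"), with 20% of infants assumed to be in pairs. If the balancing arm is always chosen, about 87–88% of pairs are split. If it is chosen with probability 0.9, 0.8 or 0.7, the shares are 76%, 67% and 60%. Balancing within center-by-age cells instead of on the margins gave 80% down to 62% over the same probabilities. The article does not state the probability, so 60–88% is used.

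**4. Size for the treatment comparison.** f and ρ are assumptions: f = 0.1–0.3 (about 10 to 31 pairs among 206 infants) and ρ = 0.1–0.6. Actual α = 2·[1 − Φ(1.96 / SE ratio)].

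| f | ρ | q | Variance factor | True SE / stated SE | Actual α |
|---|---|---|---|---|---|
| 0.1 | 0.1 | 0.60 | 1 − 0.01·0.20 = 0.998 | 0.999 | 0.050 |
| 0.2 | 0.4 | 0.60 | 1 − 0.08·0.20 = 0.984 | 0.992 | 0.048 |
| 0.2 | 0.3 | 0.87 | 1 − 0.06·0.74 = 0.956 | 0.978 | 0.045 |
| 0.2 | 0.4 | 0.88 | 1 − 0.08·0.76 = 0.939 | 0.969 | 0.043 |
| 0.3 | 0.6 | 0.88 | 1 − 0.18·0.76 = 0.863 | 0.929 | 0.035 |

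The correct limits are thus from 0.1% to about 7% narrower than the stated ones. At 50% versus 30% with 103 per arm, the 95% half-width under independence is 1.96·√(0.46/103) = 13.1 percentage points. The second row shortens it by about 0.1 point, the fourth by about 0.4 and the last by about 0.9.

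**5. Check by simulation.** With correlated binary outcomes, 103 per arm, 40% in both arms and Pearson's test, the type I error was 0.051 with no pairs, 0.049 at f = 0.2, ρ = 0.3 with 80% split, and 0.036 at f = 0.3, ρ = 0.5 with all pairs split. Power at 50% versus 30% did not fall: 0.846, 0.850 and 0.859 in the same order.

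**6. Predictors that siblings share.** For a covariate with the same value in both siblings, allocation gives no cancellation. Its variance is understated by roughly 1 + f·ρ, with ρ now the correlation left after adjustment. For example, f = 0.2 and ρ = 0.3 give 1.06, so the true standard error is about 3% larger than reported.

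**The case against.** The strongest reply is that a journal article condenses a fuller protocol, and that a sibling rule or a clustered analysis may be found there or in an analysis plan. That is possible, and silence about siblings would not by itself be a finding. But this article does fix the tests and the type of confidence limit, and it fixes an allocation that tends to separate siblings. Followed as written, the two do not fit together for any siblings enrolled.

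A second reply is that the size rests wholly on assumptions. This stands. Both siblings must breathe spontaneously at birth, avoid delivery-room intubation and fail nCPAP within 24 hours, which lowers f. Gestational age and antenatal steroids are already covariates, so the correlation left in the adjusted model should be below the marginal one. A strong random element in the minimization brings the split towards 50%, where the error in the treatment comparison vanishes. The near-null end of the range is therefore quite possible.

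A third reply is that the direction is harmless for the primary comparison. This also stands. A reader might infer from ignored clustering that false positives become more likely. That would require siblings to be kept mostly in one arm, which the article nowhere provides for and which minimization on shared factors works against.

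**Conclusion.** The point holds as a small refinement. Siblings are not excluded, are allocated individually on factors they share, and would be analysed as if independent. Under the assumed ranges (10–30% of infants in pairs, correlation 0.1–0.6, 60–88% of pairs split), the true standard error of the treatment effect is about 0.93 to just under 1.00 of the reported one. That is a slight conservatism: limits a little too wide, no inflation of the type I error and no loss of the planned power. None of the three inputs is in the article, so the range shows what could happen and does not estimate what will.

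The one place where the error runs the other way is the regression's assessment of gestational age and antenatal steroids, whose variance would tend to be understated. Nor do the documents support a conclusion that 206 infants are too few because of siblings: with pairs mostly split, the effective information on treatment is, if anything, slightly larger than assumed.

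**What to change.** - Add a mother identifier to the electronic case record form now, since the Trial status section says recruitment is under way, and complete it for infants already enrolled.
- Fit the planned logistic model by GEE with an exchangeable working correlation, or with cluster-robust standard errors, clustered on mother. Single infants form clusters of one; with 10 to 31 pairs there would be 196 to 175 clusters.
- Take the unadjusted treatment comparison from the same clustered model with treatment arm as the only term, and keep Fisher's exact test as a sensitivity analysis.
- Use the same clustering for the secondary outcomes.
- State that siblings are allocated individually, and report the number of sibling sets and how many were split.

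The cost is one form field and slightly more analysis work. Neither the allocation nor the sample size needs to change. If few siblings are enrolled, the clustered and unclustered results will be nearly the same.

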### Primary outcome measure

The primary outcome is the need for mechanical ventilation within the first 3 days of life and, therefore, we consider IN-REC-SUR-E or IN-SUR-E a success if mechanical ventilation is not required and a failure if the infant needs mechanical ventilation in the first 72 h. Infants in both groups will be considered to have reached the primary outcome also when they are not extubated within 30 min after surfactant administration or when they meet the nCPAP failure criteria after extubation.

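### The article names only odds ratios as effect estimates, attached to the adjusted model, and pre-specifies no estimate with an interval on the absolute scale on which the trial was sized

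*Protocol article*

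**What the plan says.** All references are to the protocol article.

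- **Primary outcome measure.** The outcome is binary: "The primary outcome is the need for mechanical ventilation within the first 3 days of life".
- **Sample size.** The recruitment manoeuvre is assumed to lower the need for ventilation "during the first 72 h of life from 50 % [2, 5, 7] to 30" per cent. From this it follows that "103 newborns must be enrolled in each group to detect this difference as statistically significant". The planning test is Pearson's chi-square, two-sided at alpha 0.05, and the power is 80 %.
- **Statistical analysis, univariate step.** Groups are compared using "Fisher’s exact test for categorical variables". No effect measure is attached to this test. Rates and percentages are mentioned only for describing the infants' clinical characteristics.
- **Statistical analysis, multivariable step.** Treatment arm and four characteristics ("gestational age, birth weight, antenatal steroids, CRIB score) will be included in a multiple logistic regression analysis") enter one model. The next sentence is the only one in the article that names an effect measure: "Effect estimates will be expressed as odds ratios (ORs) with maximum likelihood-based 95 % confidence limits".

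Neither a risk difference nor a risk ratio is named anywhere in the article.

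**The concern.** The trial asks how far the need for ventilation falls, and it was sized on two risks 20 points apart. The one effect measure it names is on another scale and comes from a covariate-adjusted model. Three things follow.

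1. With event rates of 30 to 50 %, an odds ratio does not approximate a risk ratio. A reader who takes it as one will think the benefit larger than it is.
2. The odds ratio is non-collapsible. When prognostic covariates enter the model, the treatment odds ratio moves away from 1 even if the two arms' overall risks stay the same. The article picks its covariates because they are thought to predict ventilation, so some movement is to be expected.
3. An odds ratio alone does not fix the absolute benefit, which also depends on the control risk. The Background reports IN-SUR-E failure rates from 19 to 69 %, so the control risk is uncertain.

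What is at stake is interpretation. The estimate named in advance cannot be laid directly beside the planned 20 points, and the scale on which absolute benefit is reported is left to be chosen later.

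**Working it through.** **Inputs.** Control risk 0.50, intervention risk 0.30, 103 infants per group, 80 % power, two-sided alpha 0.05 (Sample size); 1:1 allocation (Randomisation); failure range 19 to 69 % (Background). The article does not say how strongly the covariates predict the outcome, so that is assumed below and shown as a range.

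**Step 1: the plan's own figure.** With mean risk 0.40:

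n = [1.960 × √(2 × 0.40 × 0.60) + 0.8416 × √(0.50 × 0.50 + 0.30 × 0.70)]² / 0.20² = (1.358 + 0.571)² / 0.04 ≈ 93 per group.

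With the continuity correction: (93/4) × [1 + √(1 + 4/(93 × 0.20))]² = 23.25 × 2.1023² = 102.8, that is 103 per group. The stated number is reproduced. At 103 per group the enumerated power of the two-sided Fisher exact test is 81.1 %.

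**Step 2: the planned effect on three scales.** Intervals are Wald 95 % intervals, as if the planned rates were observed exactly with 103 per group.

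- Risk difference: 0.50 − 0.30 = 20.0 points. SE = √(0.46/103) = 0.0668, so 95 % CI 6.9 to 33.1 points.
- Risk ratio: 0.30/0.50 = 0.60. SE(log) = √(0.5/51.5 + 0.7/30.9) = 0.180, so 95 % CI 0.42 to 0.85.
- Crude odds ratio: (0.30/0.70)/(0.50/0.50) = 0.43. SE(log) = √(1/25.75 + 1/21.63) = 0.292, so 95 % CI 0.24 to 0.76.

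The fall in risk is 1 − 0.60 = 40 %; the fall in odds is 1 − 0.43 = 57 %. Misreading one as the other adds 17 percentage points.

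**Step 3: what adjustment does to the odds ratio.** Take logit(risk) = a + b × arm + s × Z, with Z standard normal and s the prognostic standard deviation on the logit scale (assumed). Solve for a so that the average control risk is 0.50, then for b so that the average intervention risk is 0.30. The adjusted (conditional) odds ratio is exp(b).

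| Assumed s | Overall risks | Adjusted odds ratio |
|---|---|---|
| 0 | 50 % vs 30 % | 0.43 |
| 0.5 | 50 % vs 30 % | 0.41 |
| 1.0 | 50 % vs 30 % | 0.36 |
| 1.5 | 50 % vs 30 % | 0.30 |
| 2.0 | 50 % vs 30 % | 0.25 |

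The risk difference is 20 points in every row.

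**Step 4: what a fixed crude odds ratio of 0.43 means in absolute terms.** Intervention odds = (3/7) × control odds, converted back to a risk.

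| Control risk | Intervention risk | Risk difference (points) | Risk ratio |
|---|---|---|---|
| 19 % | 9.1 % | 9.9 | 0.48 |
| 30 % | 15.5 % | 14.5 | 0.52 |
| 40 % | 22.2 % | 17.8 | 0.56 |
| 50 % | 30.0 % | 20.0 | 0.60 |
| 60 % | 39.1 % | 20.9 | 0.65 |
| 69 % | 48.8 % | 20.2 | 0.71 |

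**The case against.** The strongest reply is that nothing in the article is wrong. An odds ratio with a 95 % interval from logistic regression is standard for a binary outcome. A conditional odds ratio is a legitimate quantity, and non-collapsibility is not bias. Two planned risks define an odds ratio of 0.43 as fully as a difference of 20 points. The arm counts needed for Fisher's test give a crude risk difference directly. The fuller analysis plan is not shown and may name further measures. For control risks between 40 and 69 %, an odds ratio of 0.43 corresponds to a difference of 17.8 to 20.9 points, close to the plan.

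Most of this stands, and it rules out several stronger readings that a reader might infer:

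- *The result cannot be compared with the plan.* Not supported: the plan implies a crude odds ratio of 0.43, and a crude risk difference follows from the 2 × 2 table.
- *No interval on the absolute scale would be available.* Not supported: the same table yields one (step 2). It is only not pre-specified in the article.
- *The effect will look larger than it is.* True only for a reader who takes the odds ratio as a risk ratio.
- *The adjusted odds ratio is the headline result.* The article does not say so. It lists the univariate comparison first and the model after it.
- *The odds ratio is the only measure the trial plans.* This can be said of the article alone.

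One part of the reply does not hold. This is not simply a detail left to a later document: the article chooses an effect measure, ties it to the adjusted model, and that measure is not on the scale of its own sample-size assumption.

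**Conclusion.** The point holds as a matter of reporting and interpretation. The article names only odds ratios, attached to an adjusted model, for an outcome with planned risks of 30 to 50 %. It pre-specifies no estimate with an interval on the scale on which it was sized.

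Its size at the planned rates is an odds ratio of 0.43 against a risk ratio of 0.60. That gap follows from the article's own figures. The further shift of the adjusted odds ratio, to between 0.41 and 0.30, rests on assumed prognostic standard deviations of 0.5 to 1.5 and a normal covariate score. Its direction is expected if the chosen covariates are prognostic; its amount is unknown.

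The validity of the test and the planned 206 infants are unaffected. This is a worthwhile, inexpensive improvement, and the odds ratio itself is not an error.

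**What to change.** In the Statistical analysis section, state that the effect on the primary outcome will be given as a risk difference, together with a risk ratio, each with a 95 % confidence interval, and that the adjusted odds ratio is supportive.

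One way to obtain both is to standardise the logistic model already planned. Predict each randomised infant's risk twice, once with each arm assigned and the infant's own covariates kept. Average each set of predictions over all randomised infants, then take the difference and the ratio of the two averages. A delta-method or bootstrap interval will serve. The result uses the planned covariates and sits on the same scale as the planned 20 points.

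The cost is a sentence or two of wording and a few lines of code, with no new data and no more infants. Giving risk differences for binary secondary and safety outcomes as well is optional and not part of this point.
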